### Implementation Plan

To ensure successful implementation of the app across Canada, the project team includes an experienced health technology partner and multiple stakeholder representatives (end users, researchers, treatment providers, health system decision-makers) who will work collaboratively to review results and make design decisions at every step, assist in driving implementation during and post project, and evaluate the quality of the implementation process. Our technology partner, BrainFx, Inc., will lead the app’s commercialization including ongoing collaboration with the implementation team for maintenance, updates, and enhancements that will continue to keep the app relevant and responsive beyond the project. In addition to their experience in developing and commercializing a digital clinical assessment tool (BrainFx 360), they provide expertise in neurofunctional assessment and in advanced analytics to support ongoing improvement and customization of the app for different cognitive profiles. Treatment providers represent 5 test sites that were chosen based upon their varied geographic location (eg, rural vs urban), type of setting (eg, community vs psychiatric hospital vs general hospital with psychiatric division), specialization (eg, generalist clinics vs mood and anxiety specialization; psychiatric hospital vs youth-focused hospital), and interprofessional staffing (eg, psychiatrist, psychologists, nurses, social workers). These variations will facilitate the identification of implementation barriers and generalization of the results from the present study to other locations. The test sites have also been chosen for their commitment and ability to embed and sustain the app in their current practice based on having clinicians who practice CBT with youth who are anxious and/or depressed. They include the Centre for Addiction and Mental Health (Toronto, ON), Canadian Mental Health Association (York Region & South Simcoe, ON), SickKids (Toronto, ON), Markham Stouffville Hospital (Markham, ON), and Sunnybrook Health Sciences Centre (Toronto, ON).

### Phase 1: Prototype Design and Usability Optimization in a Nontreatment Context

The purpose of Phase 1 is to design and develop a fully functional (programmed) prototype with input from adolescents and therapists who are familiar with CBT, and thus able to contribute to the design of a CBT homework app.

#### Exploratory Interviews

First, exploratory interviews will be conducted individually or in small focus groups of adolescents and of therapists to obtain participants’ views and perspectives on the requirements and features of a usable design and on issues pertaining to implementation. Participants will receive a CAD$30 gift card as an honorarium.

##### Sample

We will recruit (1) up to 10 adolescents between 12 and 18 years of age who can read and speak English, do not have a profound learning disability that could interfere with engagement in CBT, and have had some experience of CBT for anxiety and/or depressive disorders (have previously been or currently are in CBT), and (2) up to 10 CBT therapist (eg, psychologist, social worker, nurse, or occupational therapist) who have led at least 2 CBT groups for anxious and/or depressed adolescents and/or provided individual CBT to at least 5 anxious and/or depressed adolescents.

##### Procedure

Interviews with adolescents and therapists will be video and audiotaped. Following a warm-up discussion about their use of mobile apps in general (what apps are appealing, how they choose apps), adolescents and therapists will be asked about their experience with CBT homework, using a list of homework activities as a reference: what challenges were involved in doing/administering homework, what they liked and what they disliked about it, any suggestions for improving it, and whether a mobile app would be a helpful tool. To guide design decisions, they will also be asked to provide input on potential design features, such as reminders to do homework (what form, how frequent), rewards for doing exercises (what kind), tips to get unstuck, a way to get feedback and help (what kind, from app or therapist), a way to display homework at the next session, and whether therapists would like to have a separate portal (serving what functions). Similarly, they will be asked for design advice to make the app appealing to use for youth and therapists (eg, colors, navigation tools). Finally, they will be asked about the contexts in which a CBT homework app would likely be used (where, when, and how), and any concerns regarding implementation (eg, access to WiFi, privacy and security, availability of support, negative effects).

##### Data Analysis

The video and audiotapes will be transcribed and analyzed using conventional content analysis [81] to group statements into themes, issues, and suggestions in order to reveal insights, ideas, or concerns. We will review the results to settle on the design of an initial prototype. This design will then be programmed and made compatible with major operating systems (eg, Apple iOS, Android, Windows Phone) and accessible from smartphones.

#### Think Aloud Study

Next, a think aloud study will be conducted to evaluate and optimize the usability of the initial prototype through an iterative process of evaluation, modification, and re-evaluation.

##### Sample

Optimization will be conducted with a sample of up to 10 youth between 12 and 18 years of age who can read and speak English, do not have a profound learning disability, and have had some experience of CBT for anxiety and/or depressive disorders, and up to 10 CBT therapists. Participants in the exploratory interviews may be included in the think aloud sample. The sample size is based on evidence regarding the number of evaluators typically required to reach saturation (ie, to detect most usability problems, ~5) [82,83] and allows for more evaluation cycles than may be required. The sample will be distributed across iterative cycles of evaluation and improvement, each involving up to 5 evaluators whose feedback is used to modify and reprogram the prototype for the next cycle. Cycles continue as long as new problems are identified. Two cycles are often sufficient [84,85].

##### Procedure

The think aloud method [65] involves verbalizing thoughts while performing a task. It is effective for usability testing because it helps identify which interface features users find intuitive and easy to use and which require improvement and further evaluation [65]. Participants will be scheduled for individual video and audiotaped sessions with an interviewer in a quiet setting that facilitates thinking aloud. Adolescents and therapists will both be given tasks to complete with the user interface for patients (eg, finding specific pieces of information, navigating to a specific part of the app, doing an exercise). They will be instructed to verbalize their thoughts continuously as they work through the tasks, while the interviewer makes field notes of problems observed. If the prototype design includes a separate therapist interface, therapists will complete several additional tasks using that interface.

A heuristic evaluation by usability specialists will also be conducted. Up to 5 mobile app developers will be asked to inspect the user interface and independently rate the extent to which it meets established usability principles for software systems [86] (eg, error prevention, recognition and recovery from errors, aesthetic and minimalist design, help and documentation).

##### Data Analysis

Think aloud transcripts and interviewer field notes will be analyzed by performing a content analysis [87] to reveal issues with usability, such as unclear instructions, unintuitive icons, and difficult navigation sequences. Following each iterative cycle, we will review the results and modify the prototype for the next cycle. The process will culminate in a usable design that is ready for further evaluation and optimization in a clinical context.

### Phase 2: Usability Optimization in the Context of Clinical Treatment

The purpose of Phase 2 is to evaluate and improve the usability of the prototype in the context of a 12-week course of CBT treatment. Associations between cognitive profiles and user experience will be explored to better understand how to customize the app for different cognitive profiles. This phase will result in a usable app that is ready to be tested for its effectiveness.

#### Sample

An independent sample will be recruited consisting of 20 youth in CBT and their therapist **s**, distributed approximately equally across 5 clinics that provide CBT treatment for youth with anxiety and/or depression. Participants will receive a CAD$30 gift card as an honorarium. Youth will be recruited from among 12- to 18-year olds with a primary diagnosis of anxiety (general anxiety disorder, separation anxiety, social anxiety, panic disorder) and/or depression (major depressive disorder, dysthymic disorder). Informed consent will be obtained from youth, their primary caregiver, and their therapist. Youth receiving medication will be included if they were on a stable dose for approximately 6 weeks prior to and throughout participation. Those with a primary diagnosis of obsessive-compulsive disorder or post-traumatic stress disorder, and those with comorbid psychosis or substance dependence will be excluded because they require different CBT strategies from those that are the focus of this research. Those who are behind by 2 or more school grades or have a profound learning disability will be excluded, given the cognitive and verbal nature of CBT. Substance use and mild learning difficulties will not be exclusion criteria. Based on intake rates of approximately 1 per week at each clinic, we expect to recruit 5 youth per week. Interest in trying the app is expected to be high. Two evaluation cycles, each with up to 10 youth and their therapists, should be sufficient to reach saturation [82], but the sample size allows for an additional cycle if needed. Youth will be given the choice of receiving a smartphone to use or using their own. They will be compensated for the cost of a basic service plan (voice, text, Internet) for 12 weeks to use the app.

#### Sample Characteristics

To describe the sample, confirm diagnoses, and explore how individual attributes may affect the user experience, youth will be assessed using the following measures administered to them and their primary caregiver/guardian by a clinical psychology graduate student research assistant (RA) trained in the administration of the measures: the Achenbach Scales [88] to assess general symptomatology, completed by youth and caregiver; the Multidimensional Anxiety Scale for Children 2^nd^ ed. (MASC-2 [89]) completed by youth and caregiver; the Child Depression Inventory 2^nd^ ed. (CDI-2 [90]) completed by the youth; the Anxiety Disorders Interview Schedule (ADIS [91]) conducted with youth and caregiver; and selected tests from the BrainFx 360 digital clinical assessment of neurofunction [92] (performance assessment by a trained administrator focusing on complex cognitive skills: divided attention, delayed memory for auditory and visual input, mental flexibility, abstract reasoning, executive functioning skills in the areas of planning, organizing, implementing, and reviewing/reflecting). The Achenbach Scales, MASC-2, and CDI-2 will be administered in a secure Web-based format. The ADIS is a semistructured interview that will be administered either over the phone or in person according to preference. Both methods have been shown to be reliable [93]. The ADIS is the optimal research interview to assess anxiety disorders, but also includes all Diagnostic and Statistical Manual of Mental Disorders criteria for depression. In addition, information will be obtained about demographic characteristics (youth age, gender, and grade; parental education, occupation, and family income) and comfort with technology (experience with computers, smartphones, tablets, and the Internet–where used, frequency of use, comfort level).

#### Procedure

Prior to beginning CBT treatment, the RA will meet individually with youth to explain the purpose of the evaluation, describe the procedure for obtaining their feedback on the usability of the app, and administer the pretreatment assessment. Before the first therapy session, the site coordinator will meet with each youth to demonstrate how to use the app and provide contact information in the event of technical problems, and with therapists to train them on the app and how to use it to introduce and review homework. Therapists will meet with the coordinator periodically to discuss experiences and any technical issues.

The usability evaluation by youth will be done via a short weekly interview conducted upon arrival at the therapy session. The interview will focus on the app’s usability for the assignment given at the end of the previous session. We will assess the efficiency of the app, via ratings of the app’s learnability (how easy to figure out and remember what to do), ease of use (the time and number of steps it takes to operate, need for technical support), and error tolerance (how free of error messages, app’s ability to prevent/recover from use errors). We will also assess satisfaction with the app, via subjective ratings of its learnability (access to the assignment, memory and understanding of the lesson, motivation to practice, coaching and suggestions, self-monitoring of symptoms and changes), usability (how easy it was to use), and likeability (of specific design features). In addition, open-ended questions will be asked about: (1) where, when, and how the app was used (to understand context of use), (2) problems using the app (to identify usability problems), and (3) how the app supported homework completion (to understand the usefulness of the app). The final evaluation interview will include additional items focusing on overall experiences and impressions of the app, ratings of the app’s overall efficiency (learnability, ease of use, error tolerance), and overall satisfaction with the app (usefulness, usability, likeability). Open-ended questions will be asked about features most and least liked, facilitators and barriers to use, any negative experiences associated with the app (eg, intrusion on privacy or fear of such an intrusion), how much the app supported learning (ratings of support for access to assignments, memory and understanding of lessons, motivation, coaching and suggestions, self-monitoring, review of homework), and any suggestions for improvement.

The usability evaluation by therapists will be done via an interview following the final session, through open-ended questions about the usefulness of the app for reviewing and troubleshooting homework, whether there were any negative effects of using the app, and any suggestions for improvement.

A heuristic evaluation by usability specialists will also be conducted, as in Phase 1. Up to 5 mobile app developers will be asked to inspect the user interface and independently rate the extent to which it meets established usability principles for software systems [86] (eg, error prevention, recognition and recovery from errors, aesthetic and minimalist design, help and documentation).

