#### Data Analysis

Content analysis will be performed on responses to open-ended questions to reveal contexts of use, usability issues, features most and least liked, facilitators and barriers, any anticipated negative effects, usefulness of the app for homework completion, and suggestions for improvement. Responses will be summarized in narrative form and frequencies of each category will be calculated. Descriptive statistics will be performed on the Likert-type ratings to measure central tendency (mode) and variability (frequencies). The cognitive skills assessment will yield clustering profiles outlining areas of strength and challenge as compared with others, permitting an exploratory qualitative analysis of associations between cognitive profiles and the usability evaluation data. The results of the study will be used to determine whether the app is usable and safe to use in the context of treatment, and thus is ready for a clinical trial of its effectiveness and acceptability in a treatment context, and to further improve the app before proceeding.

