#### Sample Size and Power

Given the low rates of homework completion in research to date, we expect that the app will have at least a moderate effect on homework completion compared with the no-app group [28,35,36]. A power calculation, based on a comparison between 2 groups (app vs no-app) across 4 occasions (pre, post, follow-up 1, follow-up 2) for a single measure, indicates that a sample size of 35 for each group would provide power of 0.84 to detect a moderate effect size for homework completion at α = .05. To allow for dropouts [98], we will recruit 100 youth between 12 and 18 years of age (10 per group at each site). As noted earlier, treatment dropout rates can be substantial and adherence to homework is often quite low. This has been taken into account in calculating the sample size. The expectation is that compliance will be greater for the app than the no-app group. Based on previous research with youth [98], we expect a 10% rate of attrition at each of the 2 follow-ups.

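### In Phase 2, direct questions about harm from the app are scheduled only at the end of treatment, so the decision that the app is safe for the randomised trial may miss harms or learn of them late

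*Protocol article*

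**What the plan says.** All places are in the protocol article, under Phase 2: Usability Optimization in the Context of Clinical Treatment, unless stated otherwise.

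- **The decision.** Data Analysis: "The results of the study will be used to determine whether the app is usable and safe to use in the context of treatment". A positive answer makes the app ready for the clinical trial.
- **The sample.** Sample: "An independent sample will be recruited consisting of 20 youth in CBT", with their therapists, at 5 clinics. "Two evaluation cycles, each with up to 10 youth and their therapists, should be sufficient to reach saturation". Expected recruitment is 5 youth per week.
- **The exposure.** The purpose of the phase is to "evaluate and improve the usability of the prototype in the context of a 12-week course of CBT treatment".
- **Weekly youth interview.** Procedure: held on arrival at each session, about the previous assignment. It has ratings of efficiency and satisfaction and three open questions: context of use, difficulties using the app (with the stated purpose of finding usability problems), and how the app helped with homework.
- **Final youth interview.** Procedure: "The final evaluation interview will include additional items focusing on overall experiences and impressions of the app". The open questions listed after that sentence include "any negative experiences associated with the app (eg, intrusion on privacy or fear of such an intrusion".
- **Therapists.** Procedure: one interview after the final session includes a question on negative effects of the app. Therapists also meet the site coordinator periodically about their experiences and technical issues.
- **Contact route for youth.** Procedure: contact details are given for technical problems.

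The Phase 2 sections describe no interview for youth who stop CBT or stop using the app, and no symptom assessment after the pretreatment one.

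**The concern.** Safety is a declared output of Phase 2, and Overview of Approach gives protection of patients from harm as the reason for testing in stages. Yet the questions that ask directly about harm come when treatment is over. This has two consequences.

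- **Selective loss.** A youth who finds the app distressing or intrusive may stop using it or stop attending. The weekly interviews take place on arrival at sessions, so a youth who no longer attends has no described occasion on which to be asked. If leaving is related to harm, the answers that reach the decision are tilted towards youth who tolerated the app.
- **Delay.** A harm early in the course may not be asked about directly until about week 12.

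At stake is a conclusion of safety reached partly because those affected were not asked. The same evaluation protocol is reused for the app group after treatment in Phase 3 (Measures).

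**Working it through.** The plan gives no figure on this point, so there is none to reproduce. The main check sets the stated contacts side by side.

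| Contact | When | Direct question on harm? |
|---|---|---|
| Weekly youth interview | each session | No; nearest item is difficulties using the app |
| Therapist-coordinator meetings | periodic | None stated; experiences and technical issues |
| Developers' heuristic evaluation | not tied to a youth | No; inspects the interface |
| Final youth interview | end of treatment | Yes |
| Therapist interview | after final session | Yes |
| Youth who stop early | none described | None described |

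Both direct questions fall at the end, and the row for early leavers is empty.

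**Timing.** At 5 youth per week, a cycle of up to 10 fills in 10 / 5 = 2 weeks, and 20 youth in 20 / 5 = 4 weeks. With a 12-week course, everyone in a cycle has started on the prototype about 12 − 2 = 10 weeks before the first youth in it reaches a final interview.

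**Illustration of selective loss (rates assumed).** Let h be the chance that a youth has an app-related harm, and q the share of harmed youth who leave before the final interview. If every harmed youth who stays reports it, and youth are independent,

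P(at least one report among 20) = 1 − (1 − h(1 − q))^20.

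| h | q = 0 | q = 0.25 | q = 0.5 | q = 1 |
|---|---|---|---|---|
| 5% | 0.64 | 0.53 | 0.40 | 0 |
| 10% | 0.88 | 0.79 | 0.64 | 0 |
| 15% | 0.96 | 0.91 | 0.79 | 0 |

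For example, with h = 10% and q = 0.5: 1 − (1 − 0.05)^20 = 0.64.

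**Illustration of fewer respondents (dropout assumed).** Overall dropout of 0%, 15% or 30% leaves 20, 17 or 14 respondents. With no harm reported, the exact one-sided 95% upper bound on the harm rate is 1 − 0.05^(1/n): 13.9%, 16.2% and 19.3%. These bounds assume that leaving is unrelated to harm, so they do not measure the selective loss. Most of their width comes from n = 20.

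**The case against.** Several points on the other side are sound.

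- **The decision does not rest on the end questions alone.** A reader might infer that it does. Data Analysis refers to the results of the study as a whole, which include the weekly answers and the heuristic evaluation. The content analysis covers responses to open questions generally and lists negative effects among its categories, so a harm volunteered in a weekly interview could be coded. Phase 1 also tests the design outside treatment first. This stands. However, the weekly question is framed around usability, and inspection by developers cannot show how a patient was affected.
- **Harms could surface during treatment.** Therapists see the youth, review homework and meet the coordinator. It would be too strong to say that nothing can be known before week 12. This stands too, but a harm that is volunteered is not the same as one that is asked about.
- **Early leavers are not said to be excluded.** A reader might infer that they never answer. The article does not say so; it only describes no interview for them.
- **The article is condensed.** Adverse-event reporting, withdrawal contacts and interview guides may be in a full protocol that is not shown, and their absence is not criticised here. The point concerns the schedule that the article does state.
- **The dropout range has no Phase 2 source.** The remark that "treatment dropout rates can be substantial" belongs to the Phase 3 sample size, and the only attrition rate given there is 10% at each follow-up. This stands, so the figures above are illustrative.
- **Weekly questions would not stop others from starting.** A cycle fills in about two weeks, so this is largely right. The gain is earlier knowledge and fewer lost answers.
- **Phase 3 has other data.** Symptoms, diagnoses and quality of life are measured in both groups before treatment, after it and at both follow-ups, so worsening can be compared with control. The concern is therefore mainly about Phase 2.

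**Conclusion.** The concern holds in a limited form. As written, direct questions on negative experiences or effects are placed only in the final youth interview and the therapist interview after the final session, and no interview is described for youth who stop early. The results are then used to "determine whether the app is usable and safe to use in the context of treatment". Other routes may bring some harms to light, but none is stated to ask directly. The safety decision may therefore miss harms or learn of them late, especially in youth who leave before the final session.

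The direction of the bias rests on one assumption: that harmed youth are more likely than others to leave and are then not interviewed. Its size cannot be set from the documents. The illustrations range from no effect, if no harmed youth leave, to complete loss of direct reports, if all of them do. The documents do not support a claim that the safety decision is invalid or that early leavers are excluded by design.

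**What to change.** Before Phase 2 starts:

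1. Add the existing negative-experience question to the weekly youth interview, and keep it in the final interview.
2. Ask it at the last contact with any youth who stops CBT or stops using the app.
3. Raise the therapist question on negative effects at the coordinator meetings already planned, as well as after the final session.
4. State in the Phase 2 Data Analysis section that the safety decision is based on all youth who started the app, with early leavers counted and described.

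The cost is one more item in an interview already held, one brief contact per early leaver, and slightly longer weekly interviews. The change should come before Phase 2 because answers not sought at the time cannot be recovered reliably afterwards. It removes the dependence on attending the final session, but it does not reduce the imprecision that comes from having only 20 youth.
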